## Abstract

**Background:**

Acute post-partum anaemia can be associated with significant morbidity including a predisposition for postnatal depression. Lack of clear practice guidelines means a number of women are treated with multiple blood transfusions. Intravenous iron has the potential to limit the need for multiple blood transfusions but its role in the post-partum setting is unclear.

**Methods/design:**

IIBAPPA is a multi-centre randomised non-inferiority trial. Women with a primary post-partum haemorrhage (PPH) >1000 mL and resultant haemoglobin (Hb) 5.5-8.0 g/dL after resuscitation with ongoing symptomatic anaemia who are otherwise stable (no active bleeding) are eligible to participate. Patients with sepsis or conditions necessitating rapid Hb restoration are excluded. Eligible participants are randomised to receive a blood transfusion or a single dose of intravenous iron polymaltose calculated using the Ganzoni formula. Primary outcome measures include Hb, Ferritin and C-Reactive Protein levels on Day 7. Secondary outcomes evaluate (i) Hb, Ferritin and CRP levels on Day 14, 28, (ii) anaemia symptoms on Day 0, 7, 14 and 28 using structured health related quality of life questionnaires, (iii) treatment safety by assessing adverse reactions and infection endpoints and (iv) the quantitative impact of anaemia on breast feeding quality using a hospital designed questionnaire.

**Discussion:**

If equivalence in Hb and ferritin levels, symptom scores and safety endpoints is demonstrated, intravenous iron may become the preferred treatment for women with acute post-partum anaemia to minimise transfusion reactions and costs.

**Trial registration:**

Australian and New Zealand Clinical Trials Registry: ACTRN12615001370594 on 16th December, 2015 (prospective approval).

## Background

Post-partum haemorrhage (PPH) commonly complicates pregnancy and can result in acute anaemia [1]. Up to 10% of women with blood loss in excess of 1000 mL will develop severe anaemia (Hb < 8 g/dL), which can be associated with lethargy, decreased mental alertness, physical weakness, poor concentration and a predisposition to post-natal depression [2–4].

Red blood cell (RBC) transfusions have traditionally been used to manage severe anaemia in the pueperium however in the absence of clear transfusion triggers many women without severe symptoms will also receive blood transfusions. This places them at an increased risk of septicaemia, haematological reactions, delayed wound healing and thromboembolism, particularly if they receive multiple transfusions [5]. Blood products are also a scarce and costly resource [5]. Recent institutional guidelines and trial data suggest blood transfusions are likely to be appropriate in patients with Hb < 7 g/dL but not necessarily if alternative therapy is available or if the individual is clinically well compensated [5, 6].

Intravenous (IV) iron therapy has been shown to reduce the requirement for allogenic blood transfusion and can restore haemoglobin levels by an average of 2.5 g/dL at day 5 post infusion with peak effects observed at 3-6 weeks [2, 7–13]. Compared to RBC transfusions, newer iron preparations excluding dextran derivatives are cheap, display a more benign side effect profile than blood transfusions (<0.5% risk of serious adverse events, 1-3% risk of mild adverse events) and have single dosing regimens [14–16].

### Primary objectives

To determine if intravenous iron is non-inferior to RBC transfusion in correcting haemoglobin deficit, replenishing iron stores and improving clinical symptoms in women with acute post-partum anaemia without increasing the rate of adverse outcomes.

### Secondary objectives

To determine if intravenous iron is superior to RBC transfusion in improving the quality of breast-feeding in women with acute post-partum anaemia.

### Hypothesis

Intravenous iron is non-inferior to RBC transfusion in women with acute post partum anaemia in correcting Hb levels and improving clinical symptoms with no increased rate of adverse outcomes.

Intravenous iron is superior to blood transfusion in replenishing pre-pregnancy iron stores.

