### Interventions

All eligible women will be approached and given information about the intervention arms of the study ie. the blood transfusions and intravenous iron including details about the interventions themselves and other scientific and ethical considerations. Those who decline either intervention will be offered oral iron in line with standard practice. These women will be invited to participate in the trial as part of an oral iron subgroup which has an identical follow up protocol. Thse women will be administered 325 mg of oral iron daily. This is not a randomised arm of the study.

Patients in the intervention group will be randomised to receive cross-matched RBC transfusion or an IV iron polymaltose infusion. In patients allocated to RBC transfusion, Hb will be checked after each unit and given to achieve a Hb of at least 9.0 g/dL. Patients who received transfusions will be discharged on 325 mg of oral ferrous sulphate for a minimum of 4 weeks.

Iron poylmaltose was selected instead of iron carboxymaltose as it allows for individualised dose calculations and a larger dose of iron to be administered. Iron carboxymaltose, despite having a shorter infusion time, has a maximum of 1 g that can be administered within a 7 day period.

The dose of iron polymaltose will be calculated according to the Ganzoni formula: Total iron dose (mg) = body weight (kg) x (150-baseline Hb (g/dL)) × 0.24 + 500 mg, assuming a target Hb of 15.0 g/dL which allows for ongoing normal per vaginal loss during the puerperium. For those with Thalassemia minor, the target Hb will be adjusted to reflect the patients pre-pregnancy Hb. Iron will be administered as per hospital protocol which instructs slow infusion at 20-40 mL/h for the first 50 mL, increasing to 120 mL/h based on patient tolerance.

Patients will be pre-medicated with anti-histamine (10 mg cetirizine hydrochloride) and anti-emetic (metoclopramide 10 mg) 1 h prior to the iron infusion to reduce adverse reactions [18]. During the infusion patients will be monitored for adverse affects including itch and urticaria, bronchospasm/dyspnoea, back, joint or muscle pain, nausea, indigestion, abdominal pain, headache, hypotension, tachycardia, syncope, and circulatory collapse [9].

Any patient experiencing an adverse reaction will receive appropriate medical care including additional RBC transfusion if indicated. Infusion rates will be slowed in the instance of mild to moderate reactions and ceased for severe reactions.

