### Statistics

To demonstrate equivalence of the interventions in restoring Hb levels at Day 7 with 90% power at 5% significance (α = 0.025), 116 women need to be recruited to each intervention group. Based on similar studies, this assumes an acceptable difference in Hb of 1 g/dL and an expected difference of 0.7 g/dL [2, 8, 12]. Hence, the final sample size, accounting for a 10% loss to follow up, is a total of 250 women.

Participants experiencing adverse reactions will remain in the trial unless they fail to meet inclusion and exclusion criteria at any point. Data will be analysed according to the intention to treat principle. Primary outcomes and secondary binary outcomes will be analysed using one sided and two group t-tests. The incidence of adverse reactions and symptom scores will be assessed by calculating rates and 95% confidence intervals. Validity of the Post Partum Symptom Scale (PPSS) will be determined at the time of analyses as part of an embedded study and if validated, correlations between subscales and primary outcomes will be analysed.

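### The objective, hypothesis and abstract promise no increase in adverse outcomes or equivalent safety, but a trial sized on Day 7 Hb alone cannot show either at the article's own event rates

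*Protocol article*

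**What the plan says.** The primary objective asks whether iron is non-inferior in correcting the Hb deficit, replenishing iron stores and improving symptoms "without increasing the rate of adverse outcomes". The Hypothesis section repeats this: "improving clinical symptoms with no increased rate of adverse outcomes". The abstract's Discussion paragraph goes further. It opens "If equivalence in Hb and ferritin levels, symptom scores and safety endpoints is demonstrated" and continues that iron may then become the preferred treatment.

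The Statistics section sizes the trial on Hb at Day 7: "116 women need to be recruited to each intervention group", and the final sample size, "accounting for a 10% loss to follow up, is a total of 250 women". The only margin given, 1 g/dL, is for Hb. For safety the section plans this: "The incidence of adverse reactions and symptom scores will be assessed by calculating rates and 95% confidence intervals". No excess in adverse reactions is named as unacceptable.

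The only event rates in the article are in the Background, for newer iron preparations: "<0.5% risk of serious adverse events, 1-3% risk of mild adverse events". No rate is given for transfusion reactions or for infection.

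**The concern.** A claim of no increase, or of equivalence, is a claim that some stated excess has been ruled out. Here the claim sits inside the primary objective and the hypothesis, but the excess is not stated and the sample size was not chosen with it in view. When events are this rare, the likely result is very few or no events in each arm. Such a result is compatible with a several-fold excess on iron, yet it could be taken to satisfy the hypothesis as worded. The main Discussion then builds on the hypotheses being true: it would call iron a safer alternative and hopes for wide adoption. At stake is whether lack of evidence of harm is presented as evidence of comparable safety when a change of practice is recommended.

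**Working it through.** **Inputs.** Total 250 women (Statistics), allocated 1:1 (Procedures, recruitment and randomisation), so 125 per arm. Iron rates from the Background: at most 0.5% serious, 1-3% mild. Equal rates in the transfusion arm are assumed, because the article gives none.

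**The plan's own figure.** There is no sample size or power for safety to reproduce. The 116 per arm is for Hb, and the article states no SD. With one-sided α = 0.025, 90% power and a distance to the margin of 1 - 0.7 = 0.3 g/dL, n = 2(1.960 + 1.282)² × SD² / 0.3², which equals 116 when SD is about 0.705 g/dL. No adverse-event rate enters that calculation.

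**Expected serious events at 0.5%.**
- Per arm: 125 × 0.005 = 0.625.
- Chance of none in one arm: 0.995^125 = 0.53.
- Chance of none in the whole trial, with equal rates: 0.995^250 = 0.29.

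**Upper limit when an arm has no serious event** (exact, two-sided 95%): 1 - 0.025^(1/125) = 2.9%, about six times 0.5%. With 116 women it is 3.1%. This result needs no assumption about transfusion.

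**95% interval for the difference, iron minus transfusion** (Newcombe, from Wilson limits):
- 0/125 vs 0/125: each Wilson upper limit is 1.96² / (125 + 1.96²) = 3.84 / 128.84 = 2.98%, so the interval is -3.0 to +3.0 points.
- 1/125 vs 0/125: the observed difference is 0.8 points and the Wilson upper limit for 1/125 is 4.4%. The upper limit of the difference is 0.8 + (4.4 - 0.8) = 4.4 points.

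**Power to detect a doubling at 125 per arm** (two-sided 5%):

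| Rates | Fisher's exact | Normal approximation |
|---|---|---|
| 0.5% vs 1% | 0.1% | 7% |
| 1% vs 2% | 1% | 10% |
| 3% vs 6% | 12% | 21% |

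**Margin the trial could support.** With equal true rates p, 80% power and one-sided 0.025, the smallest margin is (1.960 + 0.842) × √(2p(1 - p)/125):
- p = 0.5%: 2.5 points
- p = 1%: 3.5 points
- p = 3%: 6.0 points

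These are two to five times the rate itself. For comparison, a 1-point margin for serious events at 0.5% (a margin assumed here, since the article has none) needs (2.802)² × 2 × 0.005 × 0.995 / 0.01² = 781 women per arm. The normal approximation is rough at these rates, so the exact figures above are the safer guide.

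**The case against.** Four points can be made for the plan.

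- **Safety is already handled descriptively.** Adverse reactions are listed as a secondary outcome and are to be given as rates with 95% confidence intervals, which would display the imprecision. The abstract and the main Discussion are conditional in wording, and no section says that zero or similar counts will be read as proof. This stands, and it makes the repair small. It does not remove the mismatch: the objective and hypothesis still state a result that this analysis cannot deliver. A later analysis plan could add a margin, but it could not make 125 women per arm informative about a small excess.
- **Low power for rare harms is ordinary in trials sized on efficacy.** True, and no criticism of the sample size follows. The criticism is of the claim attached to it.
- **The rates are for iron only, and infection has none.** Correct. The two-arm figures rest on that assumption and concern treatment reactions only. Fisher's test is also not a planned analysis; the normal approximation gives 21% instead of 12% for 3% vs 6%, which is still low.
- **The monitoring board has a suspension rule.** More than 2 severe reactions per 50 is above 4%, at least eight times the cited serious rate. It is a trigger for review, not a test of no increase.

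A reader might also infer that reactions are ascertained unequally, because the itemised list in Interventions ("During the infusion patients will be monitored for adverse affects including itch and urticaria") belongs to the iron infusion. The article does not support that. Monitoring/reporting of data counts anaphylaxis and haematological reactions in either group, Secondary outcomes lists adverse reactions without restricting them to one arm, and Follow up applies a checklist examination to all women. A list of transfusion reactions is a detail that a condensed article may leave to the full protocol.

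**Conclusion.** The point holds for the safety wording. The article places a confirmatory safety statement in its primary objective, hypothesis and abstract, while the design has a margin and sample size for Day 7 Hb alone. At the cited iron rates, 125 women per arm cannot exclude a several-fold excess: the upper limit is 2.9% after 0/125, the difference could be as large as +3.0 points at 0 vs 0 and +4.4 points at 1 vs 0, and Fisher power for 3% vs 6% is about 12%.

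Two limits apply. Whether 125 per arm is enough depends on a margin that the article does not give; one of 2.5 points (serious) or 3.5 to 6.0 points (mild) would be within reach, but it would be a multiple of the event rate. And the figure of about 3 points should not be taken as what the trial can exclude in general: it applies only when neither arm has a serious event, which happens in about 29% of trials at 0.5% per arm.

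**What to change.** 1. In the primary objective, the hypothesis and the abstract's Discussion, say that adverse outcomes will be described and compared by estimation. Remove the statements that they will be shown not to increase or to be equivalent.
2. In Statistics, report the between-arm difference in adverse-reaction incidence with its 95% confidence interval, using a method suited to small counts such as Newcombe's.
3. Add one sentence on what the trial can exclude: even with no serious event in either arm, an excess of up to about 3 percentage points could not be ruled out, and more if any occur in the iron arm.

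This changes wording and adds one reported estimate. Treatment, follow-up and sample size are untouched. The cost is a more modest safety claim.

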## Design

This is a multi-centre prospective, randomised, open-label, non-inferiority trial.

### Study settings

Participants will be recruited from at least three Australian hospitals, including Westmead Hospital, a tertiary teaching centre. Secondary sites are eligible if they are willing to participate and have the ability to collect and process blood tests and prepare and administer interventions according to the study protocol in a reasonable timeframe. They must be adequately staffed for recruitment, data collection (including follow-up) and treatment monitoring.

Patients will receive information about the study in antenatal clinics and recruitment will occur post-natally as hospital inpatients

### Participants/eligibility criteria

The sample population will consist of women who sustain a primary post-partum haemorrhage in excess of 1000 mL with a resultant Hb drop of ≥3 g/dL and Hb of 5.5-8.0 g/dL. Asymptomatic women, as well as patients with mild signs and/or symptoms of anaemia including dizziness, increased respiratory rate to >/= 25 on minimal exertion, HR 100-130 or a postural blood pressure drop of >10 mmHg are eligible.

Blood loss will be assessed by weighing all blood stained articles including sponges, sheets, under-pads and clothing. If delivery occurs in the operating theatre (after subtracting liquor volume) suction output will be added. Where possible all blood spillage will be mopped up, weighed and added to the total.

Evidence suggests 90% of women with PPH > 1000 mL have resultant Hb < 10 g/dL thereby defining our haemorrhage cut off [1]. Similarly the nominated minimum Hb is a conservative estimate based on levels used in previous studies evaluating expectant management in patients with acute anaemia [6, 10, 11, 17].

If applicable, enrolment must occur within 48 h of resuscitation and stabilisation. Stabilisation is defined as (1) having no active per vaginal bleeding in excess of expected post-partum losses and (2) having all vital parameters within hospital review criteria for a period of 12 h immediately prior to study recruitment (i.e. all patients having pulse <130 bpm, systolic blood pressure > 90 mmHg, diastolic blood pressure < 110 mmHg, respiration rate < 25, temperature < 38.5 degrees and oxygen saturations >90%).

Patients with significant antenatal or peri-partum complications such as severe pre-eclampsia who are now stable (as per above criteria) are eligible. Women who receive whole blood transfusion, other blood products, antibiotics (other than for sepsis) and intravenous fluid therapy prior to stabilisation will also be eligible.

### Major inclusion criteria

Age 16-50 yearsWillingness to attend follow up at Day 7, 14, 28

### Major exclusion criteria

Age < 16 or >50 yearsRefuse consent to blood transfusion or iron infusionCo-morbidities necessitating rapid Hb restoration including: cardiac failure, ischemic heart disease, chronic renal failureKnown hematological malignancyKnown hemaglobinopathies requiring regular transfusionsSepsis (clinical or laboratory evidence—intrapartum fever >38.5 degrees with abnormal vital signs, positive blood culture)Contraindications to iron polymaltose (i.e. asthma, known hypersensitivity to iron polymaltose, chronic polyarthritis, acute renal dysfunction, uncontrolled hyperparathyroidism, infectious hepatitis and iron overload (ferritin >1000 ng/L)Severe symptoms of anemia including dyspnoea at rest, angina pectoris, syncope or transient ischemic attacks.

### Interventions

All eligible women will be approached and given information about the intervention arms of the study ie. the blood transfusions and intravenous iron including details about the interventions themselves and other scientific and ethical considerations. Those who decline either intervention will be offered oral iron in line with standard practice. These women will be invited to participate in the trial as part of an oral iron subgroup which has an identical follow up protocol. Thse women will be administered 325 mg of oral iron daily. This is not a randomised arm of the study.

Patients in the intervention group will be randomised to receive cross-matched RBC transfusion or an IV iron polymaltose infusion. In patients allocated to RBC transfusion, Hb will be checked after each unit and given to achieve a Hb of at least 9.0 g/dL. Patients who received transfusions will be discharged on 325 mg of oral ferrous sulphate for a minimum of 4 weeks.

Iron poylmaltose was selected instead of iron carboxymaltose as it allows for individualised dose calculations and a larger dose of iron to be administered. Iron carboxymaltose, despite having a shorter infusion time, has a maximum of 1 g that can be administered within a 7 day period.

The dose of iron polymaltose will be calculated according to the Ganzoni formula: Total iron dose (mg) = body weight (kg) x (150-baseline Hb (g/dL)) × 0.24 + 500 mg, assuming a target Hb of 15.0 g/dL which allows for ongoing normal per vaginal loss during the puerperium. For those with Thalassemia minor, the target Hb will be adjusted to reflect the patients pre-pregnancy Hb. Iron will be administered as per hospital protocol which instructs slow infusion at 20-40 mL/h for the first 50 mL, increasing to 120 mL/h based on patient tolerance.

Patients will be pre-medicated with anti-histamine (10 mg cetirizine hydrochloride) and anti-emetic (metoclopramide 10 mg) 1 h prior to the iron infusion to reduce adverse reactions [18]. During the infusion patients will be monitored for adverse affects including itch and urticaria, bronchospasm/dyspnoea, back, joint or muscle pain, nausea, indigestion, abdominal pain, headache, hypotension, tachycardia, syncope, and circulatory collapse [9].

Any patient experiencing an adverse reaction will receive appropriate medical care including additional RBC transfusion if indicated. Infusion rates will be slowed in the instance of mild to moderate reactions and ceased for severe reactions.

A new intravenous cannula will be inserted immediately prior to treatment to minimise the risk of cofounding infection.

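### Treating the transfusion arm to a minimum Hb makes the expected Day 7 difference depend on entry Hb, and the stated unadjusted t-test would not show it

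*Protocol article*

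**What the plan says.** All references are to the protocol article.

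- **Interventions, transfusion arm:** "Hb will be checked after each unit and given to achieve a Hb of at least 9.0 g/dL". This is a minimum; no upper limit is given. These women then go home on oral iron for at least four weeks.
- **Interventions, iron arm:** "The dose of iron polymaltose will be calculated according to the Ganzoni formula", so the dose varies with weight and baseline Hb.
- **Background:** intravenous iron "can restore haemoglobin levels by an average of 2.5 g/dL at day 5 post infusion with peak effects observed at 3-6 weeks". There is no Day 7 figure and no breakdown by starting Hb.
- **Participants/eligibility criteria:** women enter "with a resultant Hb drop of ≥3 g/dL and Hb of 5.5-8.0 g/dL".
- **Statistics:** the sample size is 116 per arm at 90% power and α = 0.025, and "this assumes an acceptable difference in Hb of 1 g/dL and an expected difference of 0.7 g/dL". The direction of the 0.7 is not stated. Primary outcomes, which include the Day 7 Hb level, are to be compared by one-sided, two-group t-tests. No baseline covariate is named.
- **Procedures, recruitment and randomisation:** the only stratification factor is mode of delivery. Table 1 has Hb measured at enrolment.

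**The concern.** The two arms are built differently. Transfusion is titrated to a level, so Day 7 Hb in that arm should depend little on where a woman started. Iron is described by a rise, so Day 7 Hb in that arm should carry her starting value forward. The expected difference between arms then moves with entry Hb by design, over an entry range 2.5 g/dL wide (8.0 - 5.5) against a margin of 1 g/dL.

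A two-group t-test on Day 7 levels returns one average over whatever mix of entry Hb is recruited. If most women enter near 8.0, that average can clear the margin comfortably while women near 5.5 fall short by more than the trial's own limit. The reader of the result would have no sign of it.

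**Working it through.** **The plan's own figure.** The 116 per arm cannot be reproduced strictly, because no SD is stated. With n = 2(1.960 + 1.282)² SD² / (1 - 0.7)², n = 116 gives SD = 0.3 × √58 / 3.242 ≈ 0.705 g/dL. An SD of about 0.7 is used below as an assumption.

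**Expected difference by entry Hb.** Let b be entry Hb and s the amount by which transfused women stand above 9.0 at Day 7 (overshoot plus later recovery; an assumption, taken as the same at every b). With a constant iron rise of 2.5:

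D(b) = (b + 2.5) - (9.0 + s) = b - 6.5 - s

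D is zero at b = 6.5 + s and passes the margin below b = 5.5 + s.

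| s | D at 5.5 | D at 6.5 | D at 8.0 | zero at | beyond margin below |
|---|---|---|---|---|---|
| 0 | -1.0 | 0.0 | +1.5 | 6.5 | none in range |
| 0.5 | -1.5 | -0.5 | +1.0 | 7.0 | 6.0 |
| 0.95 | -1.95 | -0.95 | +0.55 | 7.45 | 6.45 |
| 1.5 | -2.5 | -1.5 | 0.0 | 8.0 | 7.0 |

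The row s = 0.95 is the one in which the plan's 0.7 is the mean shortfall of iron under a uniform entry Hb: mean b = 6.75, so 6.75 - 6.5 - 0.95 = -0.70. An iron rise above 2.5 by Day 7 lowers s one for one.

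**If iron works harder at low Hb.** Let the rise be 2.5 + k(6.75 - b), so that k is the extra rise per 1 g/dL lower entry Hb. Range of D from b = 5.5 to b = 8.0:

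| k | s = 0 | s = 0.5 | s = 0.95 |
|---|---|---|---|
| 0 | -1.0 to +1.5 | -1.5 to +1.0 | -1.95 to +0.55 |
| 0.25 | -0.69 to +1.19 | -1.19 to +0.69 | -1.64 to +0.24 |
| 0.5 | -0.38 to +0.88 | -0.88 to +0.38 | -1.32 to -0.07 |
| 0.8 | 0.0 to +0.5 | -0.5 to 0.0 | -0.95 to -0.45 |
| 1 | +0.25 throughout | -0.25 throughout | -0.70 throughout |

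At s = 0 the sign change goes once k reaches about 0.8. At k = 1 there is no gradient.

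**How far dosing might go towards that.** The printed formula subtracts a baseline Hb labelled g/dL from 150, and its units need reconciling (a separate matter), so both readings are shown for an assumed 70 kg.

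- Hb in g/L: 70 × (150 - 55) × 0.24 + 500 = 2096 mg at the lowest entry Hb and 70 × (150 - 80) × 0.24 + 500 = 1676 mg at the highest, 25% more at the low end. At the mid-range 67.5 g/L the dose is 1886 mg. If the rise were proportional to dose (assumption), it would be 2.5 × 2096/1886 ≈ 2.8 at 5.5 and 2.5 × 1676/1886 ≈ 2.2 at 8.0. D would then run from about -0.7 to +1.2 at s = 0 and from -1.2 to +0.7 at s = 0.5.
- Hb in g/dL as printed: 2927.6 and 2885.6 mg, only 1.5% apart.

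**Can the pooled test hide it?** Simulation with 4,000 trials per setting, 116 per arm, k = 0 and residual SD 0.7. The iron arm also carries the spread of entry Hb. A trial passes if the lower limit (1.97 SE) exceeds -1.

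| entry Hb | s | trials passing | mean D | mean D, entry < 6.5 | share < 6.5 |
|---|---|---|---|---|---|
| uniform | 0 | 100% | +0.25 | -0.50 | 40% |
| uniform | 0.5 | 100% | -0.25 | -1.00 | 40% |
| uniform | 0.95 | 74% | -0.70 | -1.45 | 40% |
| skewed high (mean 7.17) | 0.5 | 100% | +0.16 | -0.76 | 12% |
| skewed high (mean 7.17) | 0.95 | 100% | -0.28 | -1.21 | 12% |

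With residual SD 1.0, the pass rate is 53% for uniform and 99.9% for skewed entry Hb at s = 0.95. Masking thus needs s above zero, but then it can occur with a near-certain pooled pass.

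**The case against.** The strongest reply is that a pooled mean difference in a randomised trial is a valid estimand, and that covariate and subgroup analyses usually sit in an analysis plan, which is not shown here. That stands as far as it goes: a missing subgroup analysis is not the complaint. The point rests on what the Statistics section does state, a two-group t-test on Day 7 levels, for which a better method is available at almost no cost.

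Several stronger readings are tempting, and the documents do not support them.

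- *Iron will be inferior at low Hb, or the effect does change sign.* The 9.0 is a floor, the 2.5 is a day 5 average, and the dose varies with baseline Hb. With s = 0 the figures only touch -1.0, at exactly 5.5; with s = 1.5, or with k of 0.8 or more at s = 0, there is no sign change.
- *A given share of women lies beyond the margin.* Under uniform entry Hb and a constant rise, the share is 0% at s = 0 and (6.5 - 5.5)/2.5 = 40% at s = 1.0. It is an output of assumptions.
- *At entry 8.0 the margin equals the whole transfusion effect.* The 9.0 - 8.0 = 1.0 is the minimum needed to reach a floor; the effect transfusion achieves at Day 7 is not given.
- *The protocol itself treats women below 7 g/dL as a separate group.* The Background says "blood transfusions are likely to be appropriate in patients with Hb < 7 g/dL", but the same sentence goes on to qualify this where an alternative exists or the woman is well compensated. Trial participants must be stable, and severe symptoms are an exclusion.
- *The conclusion will be applied to all anaemic women.* The Abstract words it as a possibility that also depends on ferritin, symptoms and safety. The Discussion speaks of selected, haemodynamically stable women.

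**Conclusion.** The concern holds in conditional form. On the protocol's own 9.0 and 2.5, the expected Day 7 difference runs from about -1.0 to +1.5 g/dL across the entry range, 2.5 times the margin, provided that the average rise applies at every entry Hb and transfused women sit at 9.0. Overshoot would put the lowest entry values beyond the margin, while a stronger iron response at low Hb would shrink the gradient. The documents decide neither. An unadjusted pooled t-test could therefore declare non-inferiority while the most anaemic women do worse than the margin. A reader might infer that such failure is expected, but the documents show only that it is possible and that the stated analysis would not reveal it. The pooled test is not invalid. This is a worthwhile improvement to the analysis and the interpretation, not a fatal flaw.

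**What to change.** Keep the pooled non-inferiority test on Day 7 Hb as the primary conclusion and change the method behind it. Suggested wording:

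> Day 7 Hb will be compared by linear regression on treatment and baseline Hb. Non-inferiority is concluded if the lower limit of the two-sided 95% confidence interval for the adjusted difference (iron minus transfusion) lies above -1 g/dL. As a prespecified supportive analysis, a treatment-by-baseline-Hb term will be added, with baseline Hb centred at its overall mean. The estimated difference and its confidence interval will be reported across entry Hb 5.5 to 8.0 g/dL (for example below 7.0 and at 7.0 to 8.0), together with the observed rise from baseline in the transfusion arm. The pooled result will be interpreted in that light.

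The cost is a change of analysis wording; baseline Hb is already measured in every participant. Estimates at low baseline Hb will be imprecise and may temper the claim.

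No pass/fail rule by stratum is proposed. Splitting 116 per arm at 7.0 leaves about 42 to 74 per arm per stratum under uniform or upward-skewed triangular entry Hb. With SD 0.705 and a true shortfall of 0.7, power is then roughly 50% to 74%, so a stratum could fail by chance. No treatment rule changes.
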